**8. Statistical Considerations.**

Significance tests for the efficacy of the lifestyle intervention on the longitudinally gathered data at 2 and 3 months will be individually standardized by baseline values and will be evaluated using a weighted, repeated-measures analysis of variance statistical model adjusting for the effect of age. The primary aim is to estimate effect sizes for a future application. Although the sample size of 40-50 men does not provide optimal statistical power to detect treatment effects, it is feasible sample to recruit given the time and resources provided by the funding mechanism that, while accounting for a 20% attrition rate, would allow for adequate assessment of the feasibility of the intensive lifestyle intervention and obtain the effect size estimates necessary for the design of a large randomized controlled lifestyle intervention trial. Analyses will be conducted using the intention to treat principle with last value carried forward approach used to account for data missing due to participant attrition. Descriptive statistics for the feasibility measures will be calculated prospectively throughout the trial. Exploratory analyses of the direct and indirect pathways of the intervention effects on change in FL and QOL will be conducted using a structural equation modeling longitudinal panel model approach (AMOS 6.0 software; 66, 67). Panel models are ideal for analysis of hypothesized, theory-based relationships across defined periods of time. Again, while the sample size of 40-50 men is not optimal for panel analyses, it is sufficient to obtain estimates of path coefficients necessary to calculate the sample size in order to design an intervention trial that will be appropriately powered to detect meditational pathways of interest.

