**6. Research Approach and Design**

**Approach.** IDEA-P is a single-blind, 2-arm randomized controlled pilot study designed to determine the feasibility and preliminary efficacy of an intensive lifestyle exercise and dietary intervention in PC patients undergoing prolonged ADT. A total of 40-50 men undergoing ADT will be randomly assigned to receive either the lifestyle exercise and dietary intervention (n=20-25) or standard of care disease management education (n=20-25). Assessment of all functional, anthropometric, and QOL outcomes will be obtained at baseline, after completion of the intervention at 2 months, and at a follow-up visit 3 months following the baseline assessment (see Figure 2).

**
[figure not shown]
**

**6.1 Recruitment and Description of Human Subjects.** In collaboration with the OSUCCC and the

Genitourinary Oncology Disease Unit, [name] will serve as the focal point for recruitment of men for this study. His efforts in this capacity integrate the PC care for the OSUCCC and the JCH. [name] also manages a multimodality clinical effort each Wednesday at the JCH, where medical oncologists, radiotherapists, and urologists jointly manage patients. At the present time, well over 1,000 men with PC are referred to JCH each year. Under [name] direction, the OSU team has led the nation in annual number of local patient accrual to GU clinical trials among the nearly 50 participating institutions of the Cancer and Leukemia Group B (cooperative group) for the last 4 years. In 2009 and 2010 the OSU team has accrued over three times as many GU patients as any other CALGB institution. In addition, [name] research team has successfully met total accrual via local recruitment of PC patients in several investigator-initiated trials of NIH-NCI-funded diet and nutrition studies.

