• *Stage*: At enrollment, all men have stage IV disease, which is our major presentation to the medical oncology prostate program. Two groups are typical. The first involves men who usually present for initial diagnosis with minimally metastatic disease and elevated PSA and staging studies with modest nodal enlargement or bone lesions, typically asymptotic. The second group involves men we have been monitoring after local therapy, surgery or radiation, but who have a slow rise in PSA indicating failure of curative therapy. At some point in time asymptomatic metastases are noted on scans, and ADT is offered.

• *Sedentary Lifestyle:* fewer than 60 minutes of participation in structured moderate intensity physical activity each week

• *Health Status*: all participants must be free of active CVD, unstable angina, arrhythmia, or severe systemic disease that would make moderate intensity exercise participation unsafe. Men with prior CVD that have had successful intervention/treatment that are no longer have active CVD and are medically cleared to safely exercise by their physician will be eligible to participate in the study.

• *Consents*: willing to give an informed consent and sign a HIPPA authorization form.

• *Physician Medical Clearance*: all men will have medical clearance to participate in the study from a board certified internist, primary care physician, or cardiologist (for men with ongoing cardiovascular disease) prior to inclusion in the study. All participants’ treating oncologists will also provide consent for participation prior to inclusion in the study.

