**7. Outcome Measures**

***Functional Battery***. *Functional limitations*will be measured with the abbreviated Late-Life Function and Disability Inventory (LL-FDI) (51). *Functional Performance* will be assessed using 3 valid and reliable timed performance-related mobility tasks: 400 meter walk, stair-climb, and lift and carry task (26, 27, 49, 52). Assessments of *Mobility-Related Self-Efficacy* to complete each functional task will also be completed with the tests.

**Anthropometric and Strength Battery.***Muscular strength* will be assessed using standardized one-repetition maximum testing protocols for the chest press and leg extension exercises (24, 53).*Body composition* will be assessed using the Bod Pod (Life Measurement Inc, Concord, CA) whole-body air displacement plethysmography system. The Bod Pod has established validity and reliability as an objective method for estimating body composition (54). Another method study staff will use to measure body composition *and bone density* is the GE Lunar iDXA system, which has been proven to provide excellent precision in measurement of total and regional body composition (in addition to bone density) in obese (68) as well as nonobese adults (69). *Body weight* will also be measured to the nearest 0.1 kilogram using a calibrated and certified balance beam scale.

***QOL Battery.*** Global and disease-specific QOL will be assessed using valid and reliable scales including the Satisfaction with Life Scale (7), the SF-36 (55), and the Functional Assessment of Cancer Treatment-Prostate (56) (FACT-P). Pain and fatigue will also be measured with the short-form McGill Pain Questionnaire (57)and the Brief Fatigue Inventory (BFI) (58).

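### Baseline enters the efficacy analysis only through an undefined individual standardisation; read as a ratio it fails at or near zero, and read as a change score it is usually less precise than using baseline as a covariate.

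*Protocol*

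**What the plan says.** The efficacy analysis is described in one sentence of Section 8 (Statistical Considerations). The tests are made "on the longitudinally gathered data at 2 and 3 months", and these data "will be individually standardized by baseline values and will be evaluated using a weighted, repeated-measures analysis of variance statistical model". Age is the single adjustment given, and no other covariate is named. The baseline value of the outcome therefore acts on the analysis only by transforming each man's follow-up values. The transformation is not defined, and one rule is stated for the efficacy data without exception.

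The same section gives the purpose: "The primary aim is to estimate effect sizes for a future application". It also concedes that "the sample size of 40-50 men does not provide optimal statistical power to detect treatment effects". Section 6 allocates 20 to 25 men to each arm.

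The outcomes in Section 7 are of different kinds. Weight, one-repetition maximum strength and timed mobility tasks sit well away from zero. The quality-of-life battery also contains symptom scales: "Pain and fatigue will also be measured with the short-form McGill Pain Questionnaire", with fatigue on a second instrument. The appendix schedules show that the physical assessments and questionnaires are all collected at baseline in both arms, with iDXA at the clinic visit before it.

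**The concern.** The main product of this pilot is a set of effect sizes with their variability, to be used in designing a larger trial. How baseline is handled fixes the scale of those estimates and much of their precision.

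If each man's follow-up value is divided by his own baseline, a baseline of zero gives no usable value, and a small baseline gives a very large one. A few men could then drive the arm means and SDs for that outcome. If the operation is subtraction, nothing breaks, but part of the information in the baseline measurement goes unused. If the operation is scaling by a common baseline SD, baseline is not adjusted for at all. A sample of 40 to 50 men has little precision to spare, and the text does not let a reader tell which of the three applies.

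**Working it through.** **Inputs.** From the protocol: 20 men per arm (the lower figure), analysis at months 2 and 3, age the only covariate. The protocol states no power, effect size, SD, coefficient of variation (CV), correlation, alpha or scale range, so there is no figure to reproduce. Assumed: two-sided alpha 0.05, equal SDs at baseline and follow-up, r from 0.4 to 0.95, an effect of 0.7 SD, and baseline CV 20% or 50%. Power is for a single follow-up with complete data.

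**Step 1: change score against baseline adjustment.** In units of the follow-up variance, the change score has variance 2(1 − r) and ANCOVA has 1 − r². Their ratio is 2(1 − r)/(1 − r²) = 2/(1 + r). The share of men effectively given up is 1 − (1 + r)/2.

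| r | 2(1 − r) | 1 − r² | Ratio | Share of men | Of 40 |
|---|---|---|---|---|---|
| 0.40 | 1.20 | 0.84 | 1.43 | 30% | 12 |
| 0.60 | 0.80 | 0.64 | 1.25 | 20% | 8 |
| 0.70 | 0.60 | 0.51 | 1.18 | 15% | 6 |
| 0.90 | 0.20 | 0.19 | 1.05 | 5% | 2 |
| 0.95 | 0.10 | 0.0975 | 1.03 | 2.5% | 1 |

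If the operation is only scaling by a baseline SD, the variance is 1, against 0.64 for ANCOVA at r = 0.6: a ratio of 1.56.

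**Step 2: power at r = 0.6.** The noncentrality is 0.7/SD × √(20/2). For change, SD = √0.8 = 0.894, which gives 2.47 and power 0.67. For ANCOVA, SD = √0.64 = 0.8, which gives 2.77 and power 0.77. Simulation with 6,000 replicates agrees: about 0.68 and 0.76.

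**Step 3: ratio to own baseline, same settings, simulated.**

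| Baseline | Power of the ratio |
|---|---|
| CV 20%, normal to lognormal baseline | about 0.60 to 0.64 |
| CV 50%, untruncated normal | about 0.18 to 0.19 |
| CV 50%, normal, floored at 10% of the mean | 0.29 |
| CV 50%, lognormal baseline | about 0.56 |
| CV 50%, lognormal baseline and follow-up | about 0.71 |

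The change score and ANCOVA hardly move across these rows. The ratio depends heavily on the shape of the baseline distribution near zero, so no single figure describes it. The untruncated normal row is an extreme, because about 60% of simulated trials then contain at least one impossible negative baseline.

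**Step 4: zero baselines.** Take an assumed 0–10 scale recorded to 0.1, with latent SD 2. A man scores zero if his latent value is below 0.05, with probability Φ((0.05 − m)/2) for latent mean m.

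| Latent mean | Share undefined | Expected men of 40 | Largest remaining ratio: median (95th percentile) |
|---|---|---|---|
| 1.5 | 23% | 9.4 | 8.0 (30) |
| 3 | 7% | 2.8 | 6.0 (28) |
| 5 | 1% | 0.3 | 3.1 (13) |

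The last column is simulated with 40 men and latent correlation 0.6.

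**Step 5: a counter-example.** With 20 per arm and an outcome whose effect and error are both fully multiplicative, the ratio did better than ANCOVA on the raw scale in simulation: 0.74 against 0.72, and 0.69 against 0.60 with more variable data.

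**The case against.** The strongest reply is that the wording is loose, division is only one reading of it, and a separate analysis plan may define the operation. A change from baseline, or scaling by a common SD, is defined at zero. That is right, and the instability holds only under division. It does not clear the text: the protocol itself fixes a standardisation with age as the only named covariate, and the other readings generally cost precision too.

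Four stronger conclusions that a reader might draw are not supported.

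- *Precision is lost for every outcome.* Outcomes that track closely within a man, as body weight plausibly does, lose 3% to 5% of variance under a change score, and a truly multiplicative outcome can favour the ratio.
- *Regression to the mean biases the result.* It acts alike in both randomised arms. It adds noise to a ratio but does not create a difference between arms.
- *The men are asymptomatic, so pain and fatigue will start near zero.* The remarks on stage in Section 6.2 concern metastatic disease and its findings on scans, not symptom scores, and Section 3 lists pain and fatigue among the variables expected to change. The zero floor of these scales is an assumption.
- *Sedentary men will have zero activity at baseline.* The criterion, "fewer than 60 minutes of participation in structured moderate intensity physical activity each week", allows zero but does not imply it on the questionnaires or accelerometer. Section 7 also places activity among the behavioural and feasibility measures, outside the efficacy outcomes of Objective 1.

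It is also fair to say that the pilot disclaims optimal power, so lower power alone contradicts nothing in it.

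**Conclusion.** The point holds in a limited form. Section 8 uses baseline only through an operation that it does not define, although every outcome's baseline is available as a covariate. Under the natural reading, division, the analysis cannot be carried out for a man who starts at zero and is unstable for men near zero. How many men this touches depends on scale floors and baseline distributions that the protocol does not give. The defect does not arise for weight, strength or timed tasks. Under the change-score reading the estimate is valid, and the case for a covariate is one of efficiency: substantial at moderate correlation, negligible at 0.90 and above.

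The sizes rest on assumed correlations, CVs, effect size and scale shape. The variance ratio 2/(1 + r) needs only equal SDs and a known r; the power figures for the ratio are illustrations with a wide range. Because estimating effect sizes is the stated primary aim and the remedy is nearly free, this should be fixed, but it is not a flaw that invalidates the trial.

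**What to change.** In Section 8, replace the standardisation with a repeated-measures model of the raw month 2 and month 3 values. Its terms are arm, visit, arm × visit, the baseline value of the same outcome, baseline × visit, and age. Where the schedule has only one of these visits, as for iDXA at week 12, this reduces to ANCOVA at that visit. If a standardised effect size is wanted for the later trial, divide the adjusted arm difference by the pooled baseline SD, not by each man's own baseline. If a ratio is wanted for a particular outcome, name the outcome, define the ratio, and confine it to measures that cannot start at zero.

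The cost is a sentence or two of text and one or two degrees of freedom (baseline and baseline × visit). No new data are needed. Little is gained for highly correlated outcomes, and a truly multiplicative outcome would be served slightly less well on the raw scale than by a ratio.

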**3. Objectives.** Androgen-deprivation therapy (ADT) is the foundation of treatment for men with metastatic prostate cancer (PC) and is now frequently incorporated into multimodality strategies for the curative treatment of locally advanced PC. Unfortunately, the catabolic effects of ADT result in loss of lean muscle mass, increased fat mass, reduced muscle strength, and lower bone mineral density. In turn, these adverse effects of ADT are linked with functional decline, frailty, and increased risk for cardiovascular disease and metabolic syndrome. Thus, PC patients endure long and lingering impacts on physical function, health status, and quality of life (QOL) that accompany ADT as a “trade-off” for more effective cancer control and extended longevity. Lifestyle modification, including change in exercise and dietary behaviors, may offset, or even reverse, the adverse effects accompanying ADT. However, empirical evidence documenting the feasibility and efficacy of implementing theory-based, personalized exercise and dietary interventions in men undergoing ADT is limited. Given the emerging clinical focus upon improvements in QOL in cancer survivorship, there is a *critical need* to identify the efficacy of intensive lifestyle interventions for countering the risk of functional decline and chronic disease in PC patients undergoing ADT.

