We can recruit men from the clinics of 4 GU medical oncologists, 5 cancer specific urologists, and 1 GU radiotherapist. Information about the study will also be provided to the Columbus Man to Man PC Support group. These recruitment procedures have resulted in successfully reaching target accrual of both minority and total participant levels in several recent PC clinical trials conducted at the OSUCCC and are evidence of the feasibility of successfully recruiting the target sample. Men will be recruited from [name] clinic and the GU Multimodality Clinic where several hundred men previously treated and cured of PC are monitored annually. To further increase the recruitment rate beyond those patients seen in clinic, we will also mail out a letter of introduction to the study to patients on ADT. We will then follow up the mail out of identified patients with a phone call follow-up. Additional recruitment strategies including flyers, newspaper advertisements, and presentations to local PC support groups will also be used. We are optimistic that we can accrue 3-5 men per month at OSU to the trial. As with all lifestyle interventions, we anticipate some attrition, and even a 20% loss to follow-up would result in a sample sufficient to evaluate the primary aims of interest.

**6.2 Inclusion Criteria**.

• *Diagnosed with PC*: histologically-defined diagnosis of PC based upon providing pathology reports and staging studies.

• *Initiating ADT*: will be undergoing a planned course of at least 3 months of ADT. The ADT is defined as: (a) Surgical castration; (b) GNRH antagonist alone; (c) GNRH antagonist with oral androgen receptor blockade, and (d) GNRH antagonist, oral androgen receptor blockade, and 5-alpha reductase inhibitors. We will not include men with only oral antiandrogen therapy such as 5-alpha reductase inhibitors alone or oral antiandrogens alone, as they do not produce castrate levels of testosterone.

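### Last value carried forward, the only handling of attrition in section 8, may bias the pilot's effect sizes in a direction that depends on who drops out and when, and overstates their precision

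*Protocol*

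**What the plan says.** Protocol section 8 fixes the handling of missing data: analyses follow the "intention to treat principle with last value carried forward approach used to account for data missing due to participant attrition". No alternative method, missing-data assumption or sensitivity analysis is given. The efficacy analysis uses months 2 and 3, expresses outcomes relative to each man's own baseline, and fits a weighted repeated-measures ANOVA adjusted for age.

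The same section justifies the 40 to 50 men "while accounting for a 20% attrition rate", and section 6.1 says that "even a 20% loss to follow-up would result in a sample sufficient to evaluate the primary aims of interest". On purpose, section 8 states: "The primary aim is to estimate effect sizes for a future application".

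On the expected course, section 3 says that "the catabolic effects of ADT result in loss of lean muscle mass, increased fat mass, reduced muscle strength, and lower bone mineral density", and that lifestyle change "may offset, or even reverse, the adverse effects accompanying ADT".

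**The concern.** Carrying a value forward treats a man who leaves as fixed at his last measurement. The protocol's rationale expects neither arm to stay still: untreated men should decline, and treated men should hold or gain. Because outcomes are expressed relative to baseline, a man lost before month 2 scores as no change at both visits. A man lost between months 2 and 3 keeps a month-2 value obtained while supervised sessions were still running, although section 6.5 makes month 3 unsupervised.

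The filled-in values are then analysed as if observed, so the standard errors credit the trial with data it does not have. Intention to treat requires that all randomised men be analysed as assigned. It does not require single imputation.

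The effect size is the main product of this pilot and is meant to set the size of the next trial. A distortion here passes straight into that calculation, and a confidence interval does not reveal it.

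**Working it through.** **The protocol's own figures.** With 20% loss, 40 × 0.8 = 32 and 50 × 0.8 = 40 men complete, or 16 to 20 per arm. Section 8 gives no alpha, power, effect size or SD, so the 40 to 50 cannot be derived further, and the protocol does not claim a power calculation.

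**Inputs from the protocol.** Carry-forward; 20% overall loss, not split by arm or time; 20 to 25 men per arm; analysis at months 2 and 3; decline on ADT and benefit from the intervention, both without figures.

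**Assumed inputs.** SD of change equal to 1 at both visits; dropout unrelated to outcome within each arm; means and dropout patterns as listed below, in SD units, written intervention/control.

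**Formulas.** In each arm let *a* be the fraction lost before month 2 (scored 0), *b* the fraction lost between months 2 and 3 (scored at month 2), and m2 and m3 the true mean changes.

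- Mean after carry-forward: M = (1 − a − b)·m3 + b·m2
- Variance: V = (1 − a − b)(1 + m3²) + b(1 + m2²) − M²
- Standardised effect: d = (M_int − M_con) / √[(V_int + V_con)/2]
- Ratio of planned to required N: (0.50/d)²

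The SD term matters because carried-forward baselines add zeros, which shrink the SD of change as well as the mean.

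**Worked line (row 1).** Means +0.3/−0.2, all 20% lost before month 2. Raw difference 0.8 × 0.3 − 0.8 × (−0.2) = 0.40. Variances 0.8 × 1.09 − 0.24² = 0.8144 and 0.8 × 1.04 − 0.16² = 0.8064, so the SD is 0.900 and d = 0.444. Ratio (0.50/0.444)² = 1.27.

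| Assumed pattern | True | Raw | SD | d | N ratio |
|---|---|---|---|---|---|
| 1. 20%/20%, all before month 2; +0.3/−0.2 | 0.50 | 0.40 | 0.900 | 0.444 | 1.27 |
| 2. 20%/20%, half before month 2; linear (m2 = ⅔·m3); +0.3/−0.2 | 0.50 | 0.433 | 0.952 | 0.455 | 1.21 |
| 3. As 2, but m2 = m3 | 0.50 | 0.45 | 0.952 | 0.473 | 1.12 |
| 4. 30%/10%, half before month 2; linear; +0.5/0 | 0.50 | 0.40 | 0.957 | 0.418 | 1.43 |
| 5. 30%/10%, half before month 2; linear; −0.5/−0.5 | 0 | +0.067 | 0.960 | 0.07 | n/a |
| 6. 20%/20%, all between months 2 and 3; 0.5 fading to 0.3 / −0.15 to −0.20 | 0.50 | 0.53 | 1.002 | 0.53 | 0.89 |

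For two-sided 5% alpha and 80% power (also assumed), row 1 moves the next trial from 63 to 80 men per arm.

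**Precision.** With 25 men per arm and 20% loss, 20 per arm are observed. A standardised difference then has a standard error of about √(2/20) = 0.316, but carry-forward counts all 25 and gives √(2/25) = 0.283. A simulation of row 1 (20,000 replicates, 25 per arm) gave a mean raw effect of 0.400 under carry-forward and 0.501 from observed data, with raw standard errors of 0.25 and 0.32.

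**Bias against sampling error.** The standard error is √(2/25) = 0.28 to √(2/20) = 0.32 for 25 to 20 men per arm. The largest shift in the table is 0.50 − 0.418 = 0.08.

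**The case against.** The strongest reply is that this is a feasibility pilot which concedes in section 8 that its power is not optimal. At 20 men per arm an observed 0.50 has an interval of 0.50 ± 1.96 × 0.316, or about −0.12 to 1.12, and a shift of 0.03 to 0.08 is small beside that. Retention will be reported descriptively, so attrition will be visible. In the balanced early-loss case the error leads to a larger next trial, not a smaller one. This stands, and it limits how serious the point is. It does not remove the point, because a wide interval shows sampling error but not bias, and the unknown direction prevents correction afterwards.

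Three stronger readings are tempting, and the protocol does not support them.

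- *A reader might infer that the effect sizes are certain to be biased, or biased in favour of the intervention.* They need not be. Equal loss with no true effect gives no bias, nor does stability among the men who leave. The table shows shifts both ways.
- *A reader might infer that N is overstated by 33% in row 2 and 56% in row 4.* Those figures, (0.50/0.433)² and (0.50/0.40)², hold the SD at 1. Allowing for the shrunken SD gives 21% and 43%.
- *A reader might take the 30%/10% split, the linear course or a 0.5 SD decline within three months as the protocol's expectation.* None is stated. The protocol describes harm from ADT without a rate, and its 20% is an overall planning figure.

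**Conclusion.** The concern holds in conditional form. The protocol itself prescribes carry-forward as the only handling of attrition, so this is not a detail left to a statistical analysis plan, and the method conflicts with the course that the protocol expects.

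The primary effect sizes may be biased, with a direction that depends on the timing and balance of dropout, and their precision is overstated. For an assumed true effect of 0.50 SD and equal 20% loss at random, rows 1 to 3 bound the dilution at about 0.44 to 0.47, an excess of 12% to 27% in the next trial's N. Unequal loss can dilute further (row 4) or create a small apparent benefit (row 5). A fading month-2 gain carried forward can inflate the effect (row 6).

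All these sizes rest on assumed means, SDs and dropout patterns. The shifts are below the pilot's sampling error but systematic, so the rule should be changed before analysis. It does not invalidate the trial.

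**What to change.** In section 8, replace carry-forward with a likelihood-based mixed model for repeated measures:

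- Limit it to baseline, month 2 and month 3. The 6-to-8-month visit should stay out of this analysis, because section 6.5 offers the standard of care arm exercise and dietary sessions after month 3.
- Put baseline in the outcome vector, with baseline means constrained equal across arms. A model with baseline as a covariate would drop men who have no post-baseline visit; this one retains them.
- Include arm-by-visit terms and age, and state that validity rests on data missing at random.
- Report the month-2 and month-3 contrasts with 95% confidence intervals, and name the SD used to standardise them.
- For iDXA, the food frequency questionnaire and diet records, which the appendix schedules only at baseline and week 12 within this window, use the same model with two time points and no carry-forward.
- Keep carry-forward at most as a sensitivity analysis, and report dropout by arm and by time.

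The cost is new wording in section 8 and standard software, with no new data. The downside is small: wider intervals, which reflect the data actually observed, and reliance on the missing-at-random assumption.
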